### Trial Aims

1. To track maturation of intraoral vacuum and SSB coordination as well as physiological stability of breastfeeding preterm infants over time and determine if this is related to increased effectiveness and efficiency of breastfeeding. We hypothesize that improvement in breastfeeding efficiency (mL/min) and effectiveness (total mL transferred) will be associated with changes in one or more of vacuum strength (average and changes across a feed), consistency of sucking (number of sucks/suck bursts per feed) and SSB coordination.
2. To explore the effect of the volume of milk in the breast on milk transfer during breastfeeding at 34 weeks CGA. Our hypothesis is that more milk in the breast will result in a higher volume of milk being transferred by the infant at the breastfeed.
3. (Optional) To explore the effect of nipple shield use on milk transfer at 35 weeks CGA. The hypothesis is that nipple shields improve attachment and breastmilk transfer
2. To compare SSB coordination and maturation during breastfeeding with bottle feeding with a Calmita teat, and bottle-feeding with a conventional teat. Our hypothesis is that infants fed with a Calmita teat will experience less apnoea and bradycardia and reach full oral feeds more rapidly than those fed with a standard teat.
3. To determine the effect of a vacuum triggered teat (Calmita during stay in study hospital, and Calma used for top up feeds post discharge/transfer from the study hospital) on the timing of achievement of full breastfeeding and on breastfeeding duration.

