### Trial Design

#### Trial endpoints

The primary endpoint for this trial is total breastfeed volume (mL) transferred at a breastfeed, measured at 33, 34, 35 weeks and term CGA

Secondary endpoints to be measured during monitored feeds are  
efficiency (mL/min)

- total suck duration

- total suck bursts
- mean, peak and baseline intraoral vacuum (mmHg)
- oxygen saturation range
- heart rate range
- incidence of bradycardia
- incidence of oxygen desaturation

The following feeding endpoints will also be determined

- timing of achievement of full oral feeds
- timing of achievement of full breastfeeding
- breastfeeding duration (monitored up to 3 months post-term)

1. A randomized controlled clinical trial will be undertaken with random allocation in blocks of size 4 to either a control group or an intervention group. Study design is depicted in Figure 1.
2. A pilot study of up to 5 infants will be completed prior to commencement of the trial to test and refine the set-up and duration of monitoring sessions.
3. Study participant data and milk samples will be re-identifiable, with an identification code assigned to each infant. A master sheet that matches infant identity to identification codes will be stored in a password-protected electronic file on a lap top computer. All paper copies of case report forms will be stored in a locked filing cabinet at The University of Western Australia.
4. The effect of a vacuum-controlled bottle-feeding teat (Calmita and Calma teats, Medela AG) on breastfeeding outcomes will be evaluated in this clinical trial. A shut-off valve is incorporated into the Calmita teat so milk flows only when the infant creates a vacuum. Venting prevents collapse of the teat. There are two versions of Calmita with different threshold levels for the vacuum-controlled valve of  $-10 \pm 5$  mmHg (starter teat) and  $-30 \pm 15$  mmHg (advanced teat). We have previously investigated a prototype of this product but wish to carry out more extensive studies on the final product.

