#### **Data collection techniques, participant tasks and time involved**

Monitoring of weekly daytime breastfeeds will not require extra time for the mother or infant and will last from 15 to 60 minutes depending upon the feed duration. The following data collection techniques are used:

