### Statistical analysis, data management, and record keeping

The primary outcome measure for this study is the total volume transferred during a breastfeed. Meier reported average transfer volumes of  $18.4\text{mL} \pm 13.2$  and  $3.9\text{mL} \pm 7.0$  with and without nipple shield, respectively [11]. Samples sizes required to detect a clinically relevant effect of 5mL difference between feeds with full and empty breasts were calculated separately for these two conditions. The more conservative calculation is that the study would need 24 infants in each treatment group to have 80% power (Type I error rate  $\alpha=0.05$ ) of detecting a difference this large. Allowing for a possible dropout rate of 20%, as was observed in a similar study, 30 infants per group will need to be recruited at 33 weeks CGA. The sample size was calculated as if the data will be analysed using an independent samples *t*-test. Actual analyses will be more powerful, and thus will have power to detect smaller differences.

Using this sample size, an independent samples *t* test would have the power to detect differences in secondary outcomes equivalent to  $0.83 * \text{SD}$ . This is equivalent to differences of approximately 3.9 min total sucking duration, and 12 suck bursts per feed. As with the primary outcome, use of covariate data, repeated measurements and more powerful analytic techniques increase the likelihood of detecting smaller differences than those determined here.

Data will be analysed on an intention to treat basis using R 2.15 or later versions (The R Core Team)[12] with nlme,[13] lattice,[14] and multcomp[15] packages for linear mixed models, graphical exploration and general linear hypothesis tests, respectively. To monitor both safety and efficacy, interim analysis will be performed when complete data is available for 15 infants in each group, with p values set to  $p=0.029$  for both interim and final analyses as per Pocock (p372, [16]).

For the monitored breastfeeds, differences in milk transfer volume as well as measured sucking, physiological, and feeding variables, linear mixed effects modelling will be used, with grouping for the random effects at the participant level. Use of nipple shield (yes/no), breast fullness (full/empty) and relevant demographic variables will be considered as predictive factors.

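### The modelling text covers breastfeeds only, gives event endpoints no suitable model, and specifies no test of the hypothesis that Calmita reduces apnoea and bradycardia

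*Combined protocol and SAP*

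**What the plan says.** The fourth item of the numbered list under Trial Aims, a comparison of feeding by breast, Calmita and conventional teat, carries a between-teat hypothesis: "Our hypothesis is that infants fed with a Calmita teat will experience less apnoea and bradycardia and reach full oral feeds more rapidly" than infants given a standard teat. Bottle feeds with the allocated teat are monitored at 33, 34 and 35 weeks CGA (Table 1; Treatment of Participants).

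The secondary endpoints under Trial endpoints include "oxygen saturation range", heart rate range, "incidence of bradycardia" and incidence of desaturation. Apnoea is not in that list. It appears as a safety outcome under Assessment of Efficacy and Assessment of Safety, where it is to be recorded at each feed and examined at the interim analysis, with no method given.

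The analysis text is in Statistical analysis, data management, and record keeping. It is confined to monitored breastfeeds and, for outcomes beyond the volume of milk transferred, reads "measured sucking, physiological, and feeding variables, linear mixed effects modelling will be used". Random effects are grouped by participant. On predictors it says: "Use of nipple shield (yes/no), breast fullness (full/empty) and relevant demographic variables will be considered as predictive factors". The three R packages named are for linear mixed models, graphics and general linear hypothesis tests. No binary, count or time-to-event method is named anywhere.

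**The concern.** Three things do not fit together.

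- **Feeds and factor.** The hypothesis compares teats and the bottle feeds are monitored, but the modelling text stops at breastfeeds and does not name teat group, feed type or CGA as terms.
- **Outcome type.** Bradycardia and desaturation are physiological variables, and the only method offered for physiological variables is linear. An incidence is a yes/no result or a count, with exposure that depends on how long the feed lasts.
- **Summary.** A range is the gap between two extremes. It grows with the length of recording even when the infant is no less stable.

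At stake is the trial's main safety contrast between teats. Without a stated analysis, the choice of feeds, event definition, unit and model would be made after the data are seen. If one teat lengthens or shortens feeds, ranges and per-feed event counts will shift with no change in stability per minute.

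**Working it through.** **1. The plan's own figure.** The only figure bearing on the secondary outcomes is a detectable difference of 0.83 SD. Inputs from the statistical section: 24 per group, 80% power, α = 0.05 (two-sided assumed), independent-samples t test. Noncentrality = 0.83 × √(24/2) = 2.875 on 46 df, which gives power of 80.4%. The figure reproduces (the exact detectable difference is 0.826 SD), and 24/(1 − 0.20) = 30 per group. It describes a continuous outcome only.

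**2. What that sample offers for events.** The documents give no event rates. I assumed that 10% to 50% of control infants have an event, that Calmita halves this, and that each infant contributes one yes/no result. With d = p₁ − p₂ and p̄ = (p₁ + p₂)/2,

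power = Φ[(d − z·se₀)/se₁], se₀ = √(2p̄(1 − p̄)/n), se₁ = √((p₁(1 − p₁) + p₂(1 − p₂))/n).

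For 20% vs 10% with n = 24: se₀ = √(0.15 × 0.85 × 2/24) = 0.1031; se₁ = √((0.16 + 0.09)/24) = 0.1021; (0.10 − 1.96 × 0.1031)/0.1021 = −1.00; power 15.9%.

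| Control vs Calmita | Power, α = 0.05 | Power, α = 0.029 | n per group for 80% power (α = 0.05) |
|---|---|---|---|
| 10% vs 5% | 9.5% | 6.3% | 435 |
| 20% vs 10% | 15.9% | 11.0% | 199 |
| 30% vs 15% | 23.3% | 17.0% | 121 |
| 40% vs 20% | 32.3% | 24.6% | 82 |
| 50% vs 25% | 43.0% | 34.1% | 58 |

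The 0.029 column uses the level that the plan sets for each of its two looks. The 0.83 SD figure therefore says little about what the trial can show for events.

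**3. Does a linear test on events mislead?** Simulation under assumed values: 24 infants per arm, 3 feeds each, yes/no events from a random-intercept logistic model (SD 1), equal feed lengths, and a t test on infant means. Type I error at nominal 5% was 4.4% at an event rate of 4.5%, and 5.0% to 5.1% at rates of about 11% to 40%. In this balanced case the linear test did not inflate error.

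That simulation did not vary feed length. For counts, expected events per feed = rate per minute × minutes. At the same rate, assumed mean feeds of 30 and 20 minutes give a ratio of 30/20 = 1.5 in events per feed.

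**4. Ranges and recording time.** For n independent normal readings, the expected range in SD units is ∫[1 − Φ(x)ⁿ − (1 − Φ(x))ⁿ]dx.

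- n = 15: 3.472; n = 60: 4.639; ratio 4.639/3.472 = 1.34.
- n = 20: 3.735; n = 30: 4.086; ratio 4.086/3.735 = 1.09.

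The 15 and 60 come from the section on data collection techniques, where monitoring "will last from 15 to 60 minutes depending upon the feed duration". That sentence concerns breastfeeds. One reading per minute, independence and normality are my assumptions.

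**The case against.** The strongest reply is that the plan omits detail rather than choosing a wrong method. Analysis is declared to be by intention to treat, so a comparison by arm is plainly meant. No sentence says in words that incidences go into the linear model; that is inferred from the word for physiological variables and from the package list. Incidences are listed apart from the ranges, and the research nurse records each episode. All of this stands, and it limits the point to what the text leaves unspecified. It does not remove the point: followed as written, the plan provides a Gaussian model for event outcomes at breastfeeds and nothing for bottle feeds.

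Several stronger readings are tempting, and the documents do not support them:

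- *The teat hypothesis is tested on the wrong feeds with the wrong model.* No test of it is specified at all. Nor are the ranges the planned measure for it.
- *Linear models on these events give invalid intervals.* The simulation above does not show this. It did not examine interval coverage under an effect, but nothing else in hand supports the claim. The documents also do not say that events are rare.
- *The ranges would be biased by 34% between teats.* That compares the extremes of individual breastfeed lengths. Arm bias depends on the difference in mean length: 20 vs 30 minutes gives about 9%.
- *Times to full feeding and breastfeeding duration would be analysed linearly.* They are not measurements at a monitored breastfeed, and no method is stated for them.

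It is also fair to say that adjusting for feed minutes is not obviously right. Feed length arises after randomisation and the teat may alter it, so events per feed is a defensible safety measure.

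**Conclusion.** The concern holds as a gap with a better method readily available. The modelling text reaches the bradycardia and desaturation endpoints only through a linear model at breastfeeds. It leaves the monitored bottle feeds and the randomised teat group without an analysis, so no test of the apnoea and bradycardia hypothesis is specified. Apnoea is also missing from the list under Trial endpoints.

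The size of any distortion cannot be fixed from the documents, because they give neither event rates nor bottle-feed length. Under the assumed rates, power to detect a halving is 9.5% to 43.0% at α = 0.05, so an inconclusive result on events would not show that the teats are equally safe. The dependence of the ranges on duration (3.47 SD at 15 readings, 4.64 SD at 60) rests on independent normal one-minute values. It matters for the teat comparison only if mean feed length differs between arms. The point should be addressed before analysis; it does not invalidate the design.

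**What to change.** - Add apnoea to the endpoint list, and define each event and the unit of analysis (the infant-feed).
- Analyse bradycardia, desaturation and apnoea on the monitored bottle feeds by randomised teat group, and separately on breastfeeds. Use a logistic mixed model for any event, or a Poisson or negative-binomial mixed model for counts, with a participant random effect and CGA as a term.
- Report events per feed and, as a second analysis, per feed minute with a log-minutes offset. Say that the two answer different questions because feed length is post-randomisation.
- Treat the heart-rate and saturation ranges as descriptive, or show them beside feed duration. Replacing them by time beyond alarm limits would go past the documents, which give no such limits and do not say that the oximetry signal is stored as a trace.
- For time to full oral feeds, time to full breastfeeding and breastfeeding duration, name Kaplan-Meier and Cox analyses with censoring at last contact.

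The cost is analysis wording and slightly more analysis work. Feed duration must be captured for bottle feeds as well; the monitored-feed form in Appendix E, as reproduced, shows no field for it. The events have only a free-text entry there, so a structured count would help. Low power for sparse events remains and should be stated.

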## Treatment of Participants

1. When the mother is not available to breastfeed, control group infants will use a conventional teat for suck feeds whereas the interventional group infants will use the Calmita teat. The starter teat will be offered initially and when the infant takes full feeds from the starter teat for 48-72 hours they will then use the advanced teat.
2. Monitoring of a weekly breastfeeds and bottle feeds with the allocated teat will be performed at 33, 34 and 35 weeks CGA and involves the following
  - Weigh infant pre and post breastfeeding
  - Intraoral ultrasound
  - Continuous Intraoral vacuum measurements
  - Respiratory Inductive plethysmography
  - Continuous pulse oximetry for oxygen saturation (SaO2) and heart rate
  - (optional) Maternal pre/post breastfeed milk samples <1.0mL
  - Maternal rating of Preterm Infant Breastfeeding Behavior Scale[5] (PIBBS, Appendix A)

SSB coordination is evaluated using data from intraoral vacuum, respiration and swallowing (Respiratory Inductive Plethysmography) heart rate and oxygen saturation obtained throughout the entire breastfeed[6].

3. Test weights of the infant pre and post feed, for all feeds, will be made to determine milk intake and allow calculation of top up feeds. For monitored feeds, pre and post feed milk samples (<1.0mL) will be collected and fat content measured to provide a further estimate of breast fullness.
4. At each monitored breastfeed the Preterm Infant Breastfeeding Behavior Scale[5] (PIBBS, Appendix A) will be completed by the mother.
5. In the study setting it is assumed that most stable preterm infants are offered (at least daily) breastfeeding experiences from 32 weeks CGA. A weekly breastfeed will be monitored from 33 weeks CGA. At 34 weeks CGA each infant will have up to 2 breastfeeds and one bottle-feed monitored in random order on 2-3 consecutive days with a full or empty breast. A full breast is one that has not been expressed for 3 hours prior to feeding and an empty breast one that has been expressed within an hour of the feed. At 35 weeks CGA those using a nipple shield will have the option of also having a monitored breastfeed without a nipple shield.
6. At 35 weeks or at discharge/transfer each infant will have 1 breastfeed monitored with or without a nipple shield depending on whether the infant is typically feeding with a shield, and one bottle-feed will be monitored. Infants

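### Grouping feeds by participant only leaves same-week feeds unlinked; if infants vary from week to week, the full-versus-empty standard error is too large

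*Combined protocol and SAP*

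**What the plan says.** The section on statistical analysis, data management and record keeping specifies a linear mixed effects model for the monitored breastfeeds, covering milk volume and the sucking, physiological and feeding measures. Its whole description of the correlation between feeds is the phrase "with grouping for the random effects at the participant level". On candidate predictors it says: "Use of nipple shield (yes/no), breast fullness (full/empty) and relevant demographic variables will be considered as predictive factors". Neither CGA week nor teat arm is in that list. The software is nlme with two companion packages, used as "packages for linear mixed models, graphical exploration and general linear hypothesis tests, respectively". No list of random terms (intercept, slope), no week level and no residual correlation is given.

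The design has two time scales. The primary endpoint, milk volume per breastfeed, is "measured at 33, 34, 35 weeks and term CGA" (Trial endpoints). Under Treatment of Participants, point 5, "each infant will have up to 2 breastfeeds and one bottle-feed monitored in random order on 2-3 consecutive days with a full or empty breast". The same point adds an option one week later: "At 35 weeks CGA those using a nipple shield will have the option of also having a monitored breastfeed without a nipple shield". So an infant can have two breastfeeds within days of each other at 34 weeks, an optional pair at 35 weeks, and single feeds at 33 weeks and term.

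**The concern.** Two feeds taken a day apart share that week's weight, maturity, milk supply and prescribed volume. Feeds at 33 weeks and at term do not. A participant random intercept gives both kinds of pair the same correlation. Whatever makes one infant's 34-week feeds differ together from its other feeds then goes into the residual, although it cancels when full and empty feeds from the same infant and week are subtracted. The test of full versus empty would use too large an error term.

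Full versus empty is the contrast on which the sample size is built. The plan says that its actual analyses will have more power than the independent-samples t-test used for sizing. This model would give away part of that gain.

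**Working it through.** **Inputs from the plan.** 24 infants per group after 20% dropout from 30 (30 x 0.8 = 24), so 48 in all; a 5 mL difference; SDs of 7.0 mL (no shield) and 13.2 mL (shield); a threshold of 0.029 at both looks. The plan states no within-infant or within-week correlation, so it has no figure of its own to reproduce here. Whether 24 follows from the quoted SDs is a separate question; I use it only as the number of completers.

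**Assumptions.** Five breastfeeds per infant: 33 weeks, 34 full, 34 empty, 35 weeks, term. The variance splits into infant (A), infant-by-week (W) and feed (F). I try A/W/F = 20/5/24, 20/9/20, 20/15/14 and 25/14/10. Each sums to 49 = 7.0². For SD 13.2 the same shares are scaled up and applied to all feeds.

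**Step 1: standard error of full versus empty.** The correct SE is sqrt(2F/48), because A and W cancel. Five feeds make 10 pairs, of which 9 span weeks. The participant-only residual therefore estimates F + 0.9W, and the ratio of model SE to correct SE is sqrt((F + 0.9W)/F). The true type I error at nominal 5% is 2[1 - Φ(1.96 x ratio)].

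| A/W/F | Ratio | Correct SE, SD 7.0 | Model SE, SD 7.0 | Type I error |
|---|---|---|---|---|
| 20/5/24 | sqrt(28.5/24) = 1.09 | 1.00 | 1.09 | 3.3% |
| 20/9/20 | sqrt(28.1/20) = 1.185 | 0.91 | 1.08 | 2.0% |
| 20/15/14 | sqrt(27.5/14) = 1.40 | 0.76 | 1.07 | 0.6% |
| 25/14/10 | sqrt(22.6/10) = 1.50 | 0.65 | 0.97 | 0.3% |

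Simulation agrees (3.2%, 2.1%, 0.6%, 0.4%). If W = 0 the ratio is 1.

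**Step 2: power at 5 mL.** Within week it is Φ(5/SE - z); participant-only it is Φ(5/SE - z x ratio), with SE the correct one and z = 1.96 for 0.05 or 2.183 for 0.029.

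At SD 7.0 the worst case is the first row: 5/1.00 - 1.96 x 1.09 = 2.86, or 99.8%. At 0.029 it is 99.6%. Both models exceed 99%.

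At SD 13.2 each SE is multiplied by 13.2/7.0 = 1.886. For 20/15/14, for example, SE = 1.44 and 5/1.44 = 3.47. Within week, 3.47 - 1.96 = 1.51 gives 93%; participant-only, 3.47 - 1.96 x 1.40 is about 0.72 and gives 77%.

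| A/W/F | SE | Participant-only, 0.05 | Within week, 0.05 | Participant-only, 0.029 | Within week, 0.029 |
|---|---|---|---|---|---|
| 20/5/24 | 1.89 | 70% | 76% | 61% | 68% |
| 20/9/20 | 1.72 | 72% | 83% | 62% | 76% |
| 20/15/14 | 1.44 | 77% | 93% | 66% | 90% |
| 25/14/10 | 1.22 | 88% | 98% | 80% | 97% |

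With estimated variances and t critical values the ranges are about 68-87% against 73-98% at 0.05, and about 59-79% against 64-97% at 0.029.

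**Step 3: teat comparisons.** For the mean of the two 34-week feeds, the correct variance per infant is A + W + F/2. The participant-only model takes it as (A + 0.1W) + (F + 0.9W)/2. The SE ratios are sqrt(34.75/37) = 0.97, sqrt(34.95/39) = 0.95, sqrt(35.25/42) = 0.92 and sqrt(37.7/44) = 0.93. True type I error is then about 5-7% at nominal 5% and about 3-4.5% at nominal 2.9%. For the mean of all five feeds both expressions equal A + 0.28W + F/5, so the ratio is 1.00. With the four time points weighted equally it is 1.00 to 1.02.

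**The case against.** The strongest reply is that the wording fixes the grouping factor, not the random terms. A participant-level slope on CGA, or an nlme residual correlation within participant, fits the sentence and would make near feeds more alike. This stands: the plan is under-specified, and a reader who infers that it states a wrong model goes too far. A slope is only a partial cure, however. From the values to which REML converges, it restores a ratio of 1.00 if the similarity comes from linear growth differences between infants. If there are true week effects (infant share 0.3 or 0.5, infant-week share 0.1 to 0.4), the full-versus-empty ratio stays at 1.07 to 1.50.

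Covariates could also absorb some week-level variation. Weight, prescribed volume and 24-hour production are on the monitored-feed form (Appendix E), and the sizing text mentions covariate data. But the predictor list names only shield, fullness and demographics.

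A reader might also infer that the teat comparison will produce extra false positives. The documents do not support that. They judge the teat on volume taken at the breast (Assessment of Efficacy) but define no teat contrast at 34 weeks alone. Only that contrast is affected, and modestly.

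Finally, a reader might infer that the 5 mL comparison becomes underpowered whatever the SD. At SD 7.0 it does not.

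**Conclusion.** The point holds for full versus empty. Under a participant-intercept reading, and if infants have week-specific variation, its SE is too large by 9% to 50% over the splits tried. The error is conservative: it costs precision and does not create false positives. The cost at 5 mL is negligible at SD 7.0. At SD 13.2, by the normal approximation in the table, it is about 6 to 17 percentage points of power at p<0.05 and 7 to 24 at the plan's 0.029.

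All of this rests on assumed variances, because the documents give no within-infant or within-week correlation. That the plan names no term linking same-week feeds is a matter of record; how much it matters is not known.

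**What to change.** In the statistical analysis section, state the random terms as infant and CGA week within infant (in nlme, `random = ~1 | infant/week`), and put CGA week in the fixed effects. Full versus empty at 34 weeks, and the optional shield pair at 35 weeks, are then tested against within-week variation.

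Add a paired within-infant full-versus-empty analysis as a sensitivity check, because the week-level variance rests mainly on the 34-week pairs. A continuous-time residual correlation would be a reasonable alternative if the team prefers it; what matters is that the choice is written down before the data are analysed.

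The cost is a line or two of text and one extra variance parameter. No new data are needed, and almost nothing is lost if the week-level variance proves to be zero.
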